### Sample Size

The sample size was determined based on the primary end point, namely the median time to the alleviation of influenza symptoms. Published studies have reported that the median time to symptom alleviation with oseltamivir is approximately 80 hours [14,15]. The assumption for KGM was informed by preliminary clinical evidence and prior clinical experience [11]. A noninferiority margin of 10 hours was prespecified with consideration of its clinical relevance and the feasibility of the trial. Under the assumptions of a 1:1 allocation ratio, a 2-sided significance level of .05, and 80% power, 78 evaluable participants were required per group. After accounting for an anticipated attrition rate of 15%, the target enrollment was set at 92 participants in each group, resulting in a total sample size of 184 participants.

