#### Primary Outcome

The primary outcome is time to clinical alleviation, defined as the interval from the first dose to sustained clinical improvement, namely body temperature returning to normal, defined as an axillary temperature of ≤37 °C, and all remaining influenza symptom scores being 0 (absent) or 1 (mild) for at least 24 hours.

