### Statistical Methods

Study data will be entered into the electronic database independently by 2 trained research staff members, and discrepancies will be resolved by cross-checking to ensure accuracy. All data will be stored in a password-protected, access-restricted electronic database, with access limited to authorized study personnel.

Data management and analysis will be performed using SAS (version 9.4; SAS Institute) according to a prespecified statistical analysis plan. Statistical significance will be defined as a 2-sided *P* value of <.05, and 95% CIs will be reported.

Continuous variables will be summarized as mean (SD) for normally distributed data or median (IQR) for nonnormally distributed data. Categorical variables will be presented as frequencies and percentages. Normality will be assessed using the Shapiro-Wilk test, and the equality of variances will be examined using the Levene test. Between-group comparisons of continuous end point will be performed using an independent-sample 2-tailed *t* test (normal data) or the Mann-Whitney *U* test (nonnormal data). Categorical outcomes will be compared with the chi-square test or Fisher exact test, as appropriate. McNemar test will be performed to evaluate paired proportions when preintervention and postintervention data are available. All analyses will be conducted on both the full-analysis and per-protocol populations. For the primary outcome, missing data will be handled using multiple imputation, following current best practices, to reduce potential bias and improve the robustness of the findings. In addition, a sensitivity analysis will be performed using complete-case (listwise deletion) analysis to examine the consistency of the results under different missing-data assumptions.

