This trial has several limitations. First, some symptoms, such as cough, often persist for 1 to 2 weeks [17]. Therefore, the 5-day follow-up period may not fully capture the resolution of all influenza-related symptoms, particularly those that extend beyond the acute phase [18]. Second, the absence of a placebo control may limit the assessment of the absolute efficacy of KGM and may lead to potential overestimation of treatment effects. Third, because this is an open-label trial, performance bias and assessment bias cannot be fully excluded, particularly for subjective symptom outcomes, even though standardized outcome definitions, validated scoring tools, and quality control procedures will be used to minimize bias. These design characteristics may affect the interpretation of the observed effect size and should be carefully considered when interpreting the study findings [19,20].

If KGM is shown to be noninferior to oseltamivir with an acceptable safety profile, the study may support its use as an alternative therapeutic option for adults with influenza and provide a basis for future confirmatory studies in broader populations and settings. The study findings are planned to be disseminated through peer-reviewed publication and academic conference presentations, which may further inform clinical practice and future research on TCM for influenza.

In summary, this protocol describes a multicenter randomized controlled trial designed to generate comparative evidence on the efficacy and safety of KGM for influenza treatment. The findings of this study are expected to clarify the therapeutic value of KGM and contribute to the evidence base for influenza management while acknowledging the limitations related to the lack of placebo control and blinding, as well as their potential impact on effect size interpretation.

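### Time to alleviation will be right-censored for many participants, but the only tests the article names cannot use censored times, and its only provisions for absent values can bias toward noninferiority

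*Protocol article*

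**What the plan says.** The Primary Outcome section sets a time-to-event measure: "The primary outcome is time to clinical alleviation, defined as the interval from the first dose to sustained clinical improvement". Improvement requires normal temperature and "all remaining influenza symptom scores being 0 (absent) or 1 (mild) for at least 24 hours". The Sample Size section plans on published studies in which "the median time to symptom alleviation with oseltamivir is approximately 80 hours", and states: "A noninferiority margin of 10 hours was prespecified". It gives no figure for KGM ("The assumption for KGM was informed by preliminary clinical evidence and prior clinical experience") and no standard deviation. The Discussion concedes that "the 5-day follow-up period may not fully capture the resolution of all influenza-related symptoms".

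For between-group comparisons, Statistical Methods names a t test or Mann-Whitney test for continuous end points, chi-square or Fisher tests for categorical outcomes, and McNemar's test for paired proportions. On absent primary values it says: "For the primary outcome, missing data will be handled using multiple imputation, following current best practices, to reduce potential bias". In addition, "a sensitivity analysis will be performed using complete-case (listwise deletion) analysis". No censoring rule, survival estimator or provision for a participant who has not recovered by the last assessment appears. A prespecified statistical analysis plan is mentioned but is not at hand.

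The end of observation is stated in two ways. Table 1 and the Discussion stop at day 5. Adherence and Concomitant Care schedules an observation 48 hours after the last dose, which is about day 7.

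**The concern.** A participant followed to the last visit without alleviation does not have a missing value. The time is known to exceed the time observed, so it is right-censored. A t test or Mann-Whitney comparison of times needs a completed number for each participant, and the only ways the article offers of dealing with an absent number are imputation and deletion.

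The direction of the error matters here. Absent values belong to the slowest recoveries. Removing them, or replacing them with draws resembling the observed, faster recoveries, cuts the tail off both arms and pulls the difference toward zero. In a superiority trial that would be conservative. In a noninferiority trial it favours the conclusion sought. The complete-case sensitivity analysis errs in the same direction, so agreement between the two analyses would give no reassurance.

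**Working it through.** **Inputs from the article.** Oseltamivir median about 80 h; margin 10 h; two-sided alpha 0.05; 80% power; 78 evaluable per arm; 15% attrition; 24 h confirmation; last assessment at day 5 (120 h) or about day 7 (168 h).

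**The article's own figure.** 78 / (1 − 0.15) = 91.8, so 92 per arm: this step reproduces. The 78 cannot be tested, because neither a standard deviation nor a KGM value is given. If the arms are assumed equal and means are compared, 78 = 2·SD²·(1.960 + 0.842)² / 10², so SD = 10·√39 / 2.802 = 22.3 h.

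**Latest confirmable onset.** 120 − 24 = 96 h with a day-5 end; 168 − 24 = 144 h with an end 48 h after the last dose. A cutoff of 120 h is shown as an intermediate case.

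**Share censored.** The article gives no distribution, so Weibull shapes k = 1, 1.5 and 2 are assumptions. In the oseltamivir arm S(t) = exp(−ln 2·(t/80)^k):
- S(96) = 0.435, 0.402, 0.369
- S(144) = 0.287, 0.188, 0.106

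A tight lognormal (sigma 0.275, SD about 23 h, close to the 22.3 h above) leaves about 25% unobserved at 96 h and 2% at 144 h.

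**False noninferiority.** Simulation with 78 per arm, medians 90 h (KGM, exactly at the margin) and 80 h. Noninferiority is declared if the upper limit of the two-sided 95% CI is below 10 h; the nominal rate is 2.5%.

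| Onset must be seen by | Complete-case t, Weibull shapes 1–2 | Complete-case t, wider set* | Multiple imputation from observed times, wider set* |
|---|---|---|---|
| 96 h | 34–42% | 34–66% | 32–64% |
| 120 h | 24–28% | 19–27% | 19–26% |
| 144 h | 16–19% | 6–19% | 6–19% |
| no cutoff | about 2% | 1–2.5% | 1–2.5% |

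*Exponential, Weibull shape 2, lognormal sigma 0.5 and 0.275. The two Weibull columns come from separate simulations, so they differ by simulation error.

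The last row shows that the inflation comes from how non-recovered participants are handled, not from the test or the margin. In the wider set, the true 10 h difference appears as 0.7–3.9 h at the 96 h cutoff and 0.9–6.8 h at 120 h. The tight lognormal gives the lowest rate at 144 h (about 5–6% across the t and Mann-Whitney-type intervals) but the highest at 96 h, so a small SD is not a general safeguard.

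**A censored-data analysis.** A bootstrap CI for the Kaplan-Meier median difference keeps false noninferiority at 0–2.6% in all settings. Its power with truly equal medians at 78 per arm is 0.1–60%, depending on distribution and cutoff. At a 96 h cutoff with a true KGM median of 90 h, the KGM median is not reached in about 18–31% of simulated trials (Weibull shapes 1–2).

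**The case against.** The best defence is that the article is a condensed protocol. It refers to a prespecified analysis plan, and censoring rules, the estimator and the imputation model are often placed there. A reader might infer that the protocol classes participants without alleviation as missing, or that its imputation ignores the lower bound. The text supports neither: it speaks only of missing data and gives no imputation model, and a model respecting the bound would avoid the bias. Nor does it tie the t test or Mann-Whitney test to the primary outcome by name.

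Those points limit the claim but do not remove it. The article is not merely silent: it lists its tests and adds a missing-data rule specific to the primary outcome, and none of these suits a censored time. An analysis plan that followed this list would inherit the problem.

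It could also be said that the Mann-Whitney test can rank non-recovered participants last. That serves a test of equality, but noninferiority needs a CI in hours. Assigning everyone the cutoff time gave t-test error of 27–41% at 96 h, 6–13% at 120 h and 3–9% at 144 h, and the matching Mann-Whitney-type (Hodges-Lehmann) interval gave 48–80%, 4–48% and 3–29%.

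Two further objections stand. The inflation rates rest on assumed distributions and on which last visit applies. The Kaplan-Meier median has real costs: it may not be estimable with a day-5 end, and its power at this sample size is low. Disclosing the short follow-up as a limitation is fair, but does not repair the analysis.

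**Conclusion.** The concern holds in this form: the stated tests do not fit the stated outcome, and the only routes the article gives for a participant without an event time can bias the comparison toward noninferiority. The direction was the same in every distribution and cutoff tried for complete-case analysis and for imputation from observed times.

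The size is conditional. With KGM exactly at the margin and Weibull shapes 1 to 2, complete-case error is about 34–42%, 24–28% and 16–19% at cutoffs of 96, 120 and 144 h. It falls to about 5–6% for a tight distribution followed to about day 7. It would be wrong to read 34–42% as the error rate of the planned primary analysis. That range is for the complete-case analysis with a day-5 end, and the imputation results apply only if the model draws from observed times without the lower bound.

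**What to change.** For the primary outcome, replace the t test or Mann-Whitney test with a censored-data analysis:

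- Censor participants not alleviated at their last symptom assessment.
- Make the Kaplan-Meier median difference primary, with its 95% CI compared with the 10 h margin. State in advance that noninferiority is not shown if the KGM median or the upper confidence limit cannot be estimated.
- Report restricted mean time to the last visit as supportive only. The 10 h margin was set for the median and does not carry over to it.
- Limit multiple imputation to true loss to follow-up, with each imputed time bounded below by that participant's last observed time. Do not rely on complete-case analysis as the robustness check.
- Reconcile the observation 48 hours after the last dose (Adherence and Concomitant Care) with the day-5 end (Table 1 and Discussion), because this sets the censoring time.

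The wording and programming cost is small: standard survival procedures, and no new type of data for the analysis itself. The real cost is power, which at 78 per arm may fall well below the stated 80%. It should be re-derived for this analysis, with the KGM assumption and the distribution stated, and then restated.

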**Secondary outcome measurements**							
	Time to onset of antipyretic effect	✓		✓		✓	
	Duration of antipyretic effect	✓		✓		✓	
	Changes in viral load in nasopharyngeal secretions	✓				✓	
	Individual influenza symptom score	✓		✓		✓	
	Total influenza symptom score	✓		✓		✓	
	Changes in the traditional Chinese medicine syndrome score compared with baseline	✓				✓	

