### AE Management

All AEs will be recorded in the case report form, investigated thoroughly, and followed up until resolution or stabilization. Severity will be graded as mild, moderate, or severe. Follow-up modalities (inpatient care, outpatient visits, home visits, and telephone contacts) will be tailored to severity and clinical need. All SAEs will be reported to the ethics committee within 24 hours. Withdrawal criteria will include the following: (1) occurrence of an SAE related to the study intervention, (2) poor compliance with the study protocol, (3) participant request to withdraw, or (4) other medical conditions deemed inappropriate for continuation by the investigators.

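### The total symptom score is scheduled at day 3 and day 5, but the named single-time-point test ignores day 3 for anyone without a final score

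*Protocol article*

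**What the plan says.** All references are to the protocol article.

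- **Test.** Statistical Methods: "Between-group comparisons of continuous end point will be performed using an independent-sample 2-tailed" t test when data are normal, with the Mann-Whitney U test otherwise. No repeated-measures or baseline-adjusted model is named.
- **Missing data.** Same section: "For the primary outcome, missing data will be handled using multiple imputation". It adds that "a sensitivity analysis will be performed using complete-case (listwise deletion) analysis". No secondary outcome is mentioned in either sentence.
- **Populations.** "All analyses will be conducted on both the full-analysis and per-protocol populations".
- **SAP.** Analysis is to proceed "according to a prespecified statistical analysis plan", which is not shown.
- **Schedule.** Table 1 lists "Total influenza symptom score" among the secondary outcomes, with ticks at baseline, day 3 and day 5. The Outcomes text defines this outcome as absolute and percentage change from baseline and names no time point for the comparison. The Adherence and Concomitant Care section instead places observations on day 1, day 3 and 48 hours after the last dose.
- **Attrition.** The Sample Size section raises 78 evaluable participants per group to 92: "After accounting for an anticipated attrition rate of 15" percent. It does not say when the losses are expected.
- **Withdrawal.** AE Management gives four reasons: "occurrence of an SAE related to the study intervention", poor compliance, the participant's own request, and other medical conditions judged unsuitable by the investigators.

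**The concern.** A two-sample test at the final visit can use only scores observed at that visit. Someone scored on day 3 who then leaves contributes nothing, although the day-3 score is partly informative about where that person was heading. Running the same test in the full-analysis and per-protocol sets does not bring the missing values back.

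This matters most if loss is selective and differs by arm. The trial is open-label, so participants know their treatment and may leave for different reasons in each arm. If KGM participants with poor day-3 scores leave more often, the remaining KGM participants look better than the whole arm. Selective loss of poor responders on oseltamivir distorts the comparison the other way. What is at stake is the credibility of one secondary outcome, the total symptom score.

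**Working it through.** **The plan's own figure.** 78 / (1 − 0.15) = 91.8, rounded up to 92 per group, 184 in total. This agrees with the article. The plan therefore allows for 92 − 78 = 14 participants per arm without evaluable data. Only those lost after day 3 have a day-3 score, so 14 is an upper bound on the participants affected here.

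**Inputs not in the article.** The day-3 to final-visit correlation (rho) and the dropout pattern are assumptions, shown as ranges. All illustrations put about 15% loss per arm after day 3. Bias is in within-arm SD units of the final score.

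**1. Loss completely at random.** With 78 final scores and 92 day-3 scores per arm, the variance of an arm mean is proportional to
- completers only: 1/78
- using day 3: (1 − rho²)/78 + rho²/92

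The ratio of standard errors is √(1 − rho² × 14/92).

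| rho | SE ratio | SE reduction | Effective n per arm (completers: 78) |
|---|---|---|---|
| 0.3 | 0.993 | 0.7% | 79 |
| 0.5 | 0.981 | 1.9% | 81 |
| 0.7 | 0.962 | 3.8% | 84 |
| 0.8 | 0.950 | 5.0% | 86 |

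There is no bias in this case.

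**2. Loss that depends on the day-3 score, moderate selection.** Simulation with 92 per arm, no true difference, 3000 trials per setting, and a log-odds slope for leaving of 0 or ±1 per SD of the day-3 score:

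| Pattern | rho | Completer bias (absolute, SD) | Two-sided 5% error, completer test | Bias using day 3 (absolute, SD) |
|---|---|---|---|---|
| Same slope in both arms | 0.5 / 0.7 | 0.002 / 0.001 | 4.9% / 5.0% | 0.003 / 0.001 |
| Slope in one arm only | 0.5 / 0.7 | 0.063 / 0.095 | 6.9% / 10.2% | 0.004 / 0.001 |
| Opposite slopes | 0.5 / 0.7 | 0.137 / 0.193 | 14.2% / 24.7% | 0.005 / 0.006 |

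**3. Near-extreme selection in one arm.** Simulation with KGM truly 0.30 SD worse (also an assumption), KGM losses mostly among high day-3 scorers, oseltamivir losses random, 4000 trials per setting:

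| rho | Completer estimate (SD) | Estimate using day 3 (SD) | Completer bias |
|---|---|---|---|
| 0.4 | 0.213 | 0.301 | 0.30 − 0.21 = 0.09 |
| 0.6 | 0.170 | 0.301 | 0.30 − 0.17 = 0.13 |
| 0.8 | 0.120 | 0.296 | 0.30 − 0.12 = 0.18 |

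Dividing bias by rho gives the implied shift in the completers' day-3 mean, for example 0.18/0.8 ≈ 0.22 SD. Removing exactly the worst 15% would shift it by about 0.27 SD. The scenario is therefore about 0.22/0.27 ≈ 80% of the maximum possible for one arm and should be read as close to a ceiling for one-arm selection.

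**The case against.** The strongest objection is that this is an omission from a condensed article. Missing-data rules for secondary outcomes commonly sit in the SAP, and the article points to one. That stands as far as it goes: the lack of such a rule is not an error, and how to handle outcomes scheduled only at baseline and day 5 (viral load, TCM syndrome score) can be left to the SAP. It does not dispose of the point, because the article does state the test. An SAP that applies that test as written, with no imputation for the scores, would compare completers only.

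Several stronger readings are tempting but not supported:

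- A reader might infer that the article excludes early leavers. It does not say so; this follows from the named test. Nor does it say that withdrawal ends data collection, or that day 5 is the time point compared.
- A reader might take the scores as planned support for the noninferiority claim. The article ties that claim to time to clinical alleviation, for which imputation is planned, and gives the scores no such role.
- A reader might assume that leavers are those doing badly. A related SAE may point that way, but a participant's request or poor compliance could equally follow recovery from a self-limiting illness. Nothing in the article shows loss that differs by arm.
- A reader might apply the loss of 14 per arm in full. The timing of the 15% is not given, and those who leave before day 3 have no day-3 score to use.

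**Conclusion.** The point holds as a modest weakness in the stated method for one secondary outcome. For a total score scheduled twice after baseline, a single-time-point two-sample test discards usable data and is open to bias if loss after day 3 differs by arm. Plausible sizes run from nothing (random loss, or the same selection in both arms), through roughly 0.06 to 0.10 SD (moderate selection in one arm, correlations 0.5 to 0.7), to about 0.18 SD (near-extreme selection in one arm, correlation 0.8). Opposite moderate selection in the two arms gives 0.14 to 0.19 SD. The gain in precision alone is small. All of this rests on assumed correlations, assumed dropout patterns and all losses falling after day 3. Arm-differential loss is possible in an open-label trial, but the document does not show it. The primary noninferiority analysis is not affected.

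**What to change.** 1. Reconcile the last assessment time. The Adherence and Concomitant Care section and Table 1 disagree (48 hours after the last dose against day 5), and the final-visit contrast cannot be defined until they agree.
2. Analyse the total symptom score with a likelihood-based repeated-measures model containing baseline score, arm, visit and arm-by-visit, using day 3 and the final visit together. Read the final-visit contrast from it. Confine this to the total score; the individual items are ordinal, 0 to 3.
3. Keep the t test or Mann-Whitney test as a completer sensitivity analysis.

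The cost is a few sentences in the analysis plan and a few lines of SAS, with no new data, and it should be fixed before analysis begins. The downside is small: the model assumes that missingness depends only on observed scores, and it still omits anyone with no post-baseline score.

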### Auditing

An independent auditing mechanism will be established to ensure data integrity and protocol compliance. Auditing will be conducted at regular intervals by the institutional clinical research center, independently of the investigators, and audit reports will be submitted to the ethics committee.

### Ethical Considerations

This study was approved by the Ethics Committee of the Affiliated Hospital of Nanjing University of Chinese Medicine (approval number 2025-NL-002-02). Written informed consent will be obtained from all participants before enrollment in accordance with the Declaration of Helsinki and Good Clinical Practice guidelines, and the model consent form is provided in Multimedia Appendix 2.

After confirming eligibility, the study physicians will explain the potential benefits and risks of the study to participants and, when applicable, their family members. Adequate time will be provided for consideration and questions. Written informed consent, including consent for the future use of biological samples, including serum, plasma, urine, and stool, will be obtained in accordance with Good Clinical Practice guidelines. These biological samples will be used specifically for exploratory analyses directly related to the study objectives, including biomarker research, virological analysis, and pharmacokinetic analysis. The intended use of each sample type and any future analyses will be clearly explained to participants during the informed consent process.

If participants wish to be informed of the study outcomes, a summary of the results will be provided to them. In line with international ethical standards, findings that involve major health concerns, have direct clinical applicability, or possess clear clinical validity will be communicated to participants during and after the study. Conversely, information that does not meet standards of scientific validity or clinical significance will not be disclosed to participants to avoid unnecessary confusion or misinterpretation.

Any substantial protocol amendments will be submitted to the ethics committee and updated in the trial registry and relevant publications, as appropriate. To protect participant confidentiality, all study data will be deidentified before analysis. No compensation will be provided to participants. No additional posttrial care will be provided; participants will continue to receive standard medical care at their treating hospital.

